## Background

Glenohumeral joint osteoarthritis is a common cause of shoulder pain, affecting up to one-third of patients aged > 60 years [1]. Surgical treatment is indicated for patients with glenohumeral arthritis who continue to experience significant symptoms despite an appropriate course of non-operative management. Shoulder arthroplasty accounts for the third most common joint replacement procedure after hip and knee arthroplasty [2]. Based on data from the National Patient Registry, the Statistical Department of the Danish National Board of Health, the use of primary shoulder replacement in Denmark increased from 12 replacements per 100,000 inhabitants in 2005 to 19 replacements per 100,000 inhabitants in 2015 [3]. Glenohumeral osteoarthritis is now the most common indication for total shoulder arthroplasty (TSA) in Denmark [3].

Many different TSA designs are available on the market. The stemless shoulder arthroplasty system with uncemented metaphyseal fixation has been used in Europe for glenohumeral osteoarthritis since 2004. The indications for anatomical stemless TSA are the same as for anatomical stemmed TSA: osteoarthritis; rheumatoid arthritis; and post-traumatic osteoarthritis or osteonecrosis.

The contraindications for anatomical stemless TSA are acute proximal humerus fracture, inadequate metaphyseal bone stock, and rotator cuff insufficiency [4, 5].

Stemless TSA has several theoretical advantages over stemmed TSA: restoring patients’ anatomy (humeral shaft angle, humeral head diameter, and lateralization); preserving humeral bone stock; and few complications in component removal should the need of a revision arthroplasty arise [6–8]. A recent review of 3360 anatomical TSAs found an overall complication rate of 10.3% [8]. Periprosthetic fractures accounted for 6.7% and humeral component loosening for 1.4% of all complications. Complications related to the stemmed humeral component can be divided into intraoperative (malpositioning, false route, periprosthetic fracture) and postoperative (loosening, migration, disassembly, periprosthetic fracture, stem fracture) complications [9]. When a revision is necessary because of infection or periprosthetic fracture, the removal of a well-fixed or cemented humeral component can be challenging and lead to bone damage [10].

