## Methods/Design

### Study design

An investigator-initiated, blinded (patient and data analyzer), non-inferiority, randomized controlled clinical trial.

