### Exclusion criteria

Previous shoulder surgery that involves the humeral head and/or the glenoid cavity.Patients with alcohol or drug abuse problems that can compromise rehabilitation and follow-up appointments as assessed by the recruiting surgeon at the first visit.Patients unable to understand instructions in Danish, follow the rehabilitation protocol, or answer the questionnaires because of physical or cognitive inabilities as evaluated by the recruiting surgeon at the first visit.Brachial plexus palsy.Patients with previous fractures around the shoulder (clavicle, scapula, and proximal humerus fractures).Patients with magnetic resonance imaging (MRI) scan-verified full thickness total tear of one or more of the rotator cuff tendons.Patients with computed tomography (CT) scan-verified glenoid retroversion ≥ 20° that does not allow glenoid component fixation without bone graft or need an augmented glenoid component [12].

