### Eligibility

Patients referred with the diagnosis of “glenohumeral osteoarthritis” will be examined by clinical examination and plain radiographs to confirm the diagnosis. In the case of glenohumeral osteoarthritis, which is to be treated with TSA, the shoulder surgeon will offer the patient participation in the trial at the first visit; the patient will be referred to routine shoulder CT and MRI scans (which are already a part of standard shoulder osteoarthritis protocol) and receive a folder with patient participant information and “Researchers rights in a health science research project.”

Patients will have time to consider participation before the next visit (approximately one month) after the first visit.

At the second visit, if the patients give their informed consent for participation in the study, they will receive three questionnaires to fill out while undisturbed in a room next door before handing them to a secretary who will check that the questionnaires are completed before the patient leaves the hospital.

The informed consent gives the primary investigator access to information about the patient’s health condition from the medical record, including data on age, sex, American Society of Anesthesiologists (ASA) score, previous shoulder operations, and results from shoulder CT and MRI scans.

All surgical interventions will be undertaken at the Zealand University Hospital Koege and Hvidovre Hospital. A two-year recruitment period from 01 March 2019 to 01 January 2022 is planned.

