### Randomization and concealment of allocation

A computerized irreversible randomization application, Research Electronic Data Capture (REDCap)© [13], will allocate patients into two equal groups:Operated with stemmed shoulder arthroplasty, Biomet Comprehensive® Total Shoulder System; andOperated with stemless shoulder arthroplasty, Biomet Comprehensive® Nano Shoulder System.

The randomization sequence will be computer-generated by block randomization (four in each block) and balanced according to age in years (18–49, 50–59, 60–69, 70–79, 80–89, 90–110), sex, and ASA score. The randomization (patient allocation) will be performed on the trial laptop computer in the operation room while the patient is being anesthetized in the preparation room next door. The operating surgeon will obtain the allocation code by logging onto the REDCap website after positioning the anesthetized patient in a beach chair position. After randomization, the patient’s allocation will be revealed to the operation team to unpack the necessary operation tools and prosthesis.

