#### Data analysis

No interim data analysis will be carried out. The primary investigator will enter data in the REDCap database, and the principle investigator before the data analysis will perform proofreading of a random sample of 20 patients.

Data analysis will be conducted by a blinded biostatistician. Patients who drop out after the three-month evaluation will be included in the analysis based on three months of data (“last observation carried forward”). Patient dropouts before the three months’ evaluation will not be included in the analysis unless they participate in the one-year questionnaire evaluation. As suggested in the extension of the CONSORT statement for non-inferiority trial design, a per-protocol analysis will be conducted and results obtained [28, 29]. A questionnaire containing one or more missing answers will be marked as incomplete; the patients will be contacted by letter to answer the missing questions.

Descriptive statistics will be used to report demographic data. Differences in demographic data and outcome measures between the two groups will be compared using chi-square test for categorical variables; parametric (Student’s t-test) or non-parametric (Mann–Whitney U-test) test for continuous variables depending on the nature of data. Data will be checked for possible extreme values before the analysis. The statistical analyses will be performed using SPSS version 25.0 (IBM Corp, Armonk, NY, USA) [30]. The level of statistical significance is set at *P* < 0.05; all *P* values are two-tailed. All complications, including glenoid and humeral component loosening, glenoid wear instability, rotator cuff tear, intraoperative and postoperative periprosthetic fracture, nerve injury, infection, deltoid injury, and deep venous thrombosis will be reported. Our sample size does not give us enough power to allow comparison.

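### Non-inferiority rests on an undefined per-protocol set, with no analysis of all randomised patients as allocated, so exclusions after randomisation may differ between arms

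*Protocol article*

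**What the plan says.** The Study design section describes the trial as "An investigator-initiated, blinded (patient and data analyzer), non-inferiority, randomized controlled clinical trial". The margin is 12.5 percentage points on the WOOS score at 12 months (Sample size and power calculation).

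On the analysis population, Data analysis says "As suggested in the extension of the CONSORT statement for non-inferiority trial design, a per-protocol analysis will be conducted and results obtained". The only other inclusion rules there concern dropout. A patient lost after three months has the three-month value carried forward. A patient lost before three months is left out unless the one-year questionnaire is answered. The section on dropout and protocol violations says only that violations are recorded and reported.

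Three further statements bear on who might leave a per-protocol set:

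- Background: "The contraindications for anatomical stemless TSA are acute proximal humerus fracture, inadequate metaphyseal bone stock, and rotator cuff insufficiency".
- Exclusion criteria: fractures around the shoulder and full-thickness cuff tears are covered, but the only bone criterion concerns the glenoid ("Patients with computed tomography (CT) scan-verified glenoid retroversion ≥ 20° that does not allow glenoid component fixation without bone graft").
- Randomization and concealment of allocation: "The operating surgeon will obtain the allocation code by logging onto the REDCap website after positioning the anesthetized patient in a beach chair position"; only then "the patient’s allocation will be revealed to the operation team to unpack the necessary operation tools and prosthesis".

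**The concern.** A per-protocol set is formed partly by what happens after randomisation. If the reasons for leaving it are tied to the implant, the groups compared are no longer those that randomisation produced. The Discussion relies on randomisation to prevent selection bias, and a sole per-protocol analysis weakens that protection.

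The bone-stock statement makes this more than a general worry. A patient with inadequate metaphyseal bone meets no exclusion criterion and can be allocated to the implant for which the Background calls that bone a contraindication. If another implant is then used, the article does not say whether the patient stays in the analysis or in which group. A counterpart allocated to the stemmed implant may be treated as allocated and kept. If such patients tend to do worse, removing them from the stemless group raises its mean and makes non-inferiority easier to declare.

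Because membership is not defined, it could also be settled after outcomes are known. That would affect the primary conclusion of the trial.

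**Working it through.** Scores are taken with higher as better, as in the Hypotheses section, so non-inferiority means that the lower limit for stemless minus stemmed lies above −12.5.

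**1. The plan's own figure.** Inputs from the sample size section: margin 12.5, SD 20.0, one-sided 95% limit, 80% power, true difference 0.

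n per arm = 2 × (1.645 + 0.842)² × 20² / 12.5² = 31.7, rounded up to 32, so 64 in total. This matches the plan. With 32 per arm, SE = 20 × √(2/32) = 5.0, and power by the noncentral t is 79.6%. The point does not disturb the sample size.

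**2. Effect of selective exclusion.** Let c be the share of patients who cannot take the stemless implant, and let them score D points below the others whichever implant they carry. Let μ be the stemmed mean in the other patients, and set the true difference in those patients at the margin, −12.5.

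- Stemless per-protocol mean: μ − 12.5 (share c removed)
- Stemmed per-protocol mean: μ − cD (share c retained)
- Difference: −12.5 + cD

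The shift toward non-inferiority is c × D. The documents give neither c nor D; both ranges below are assumptions. Type I error is from the noncentral t with SD 20, 32 stemmed patients and 32(1 − c) stemless patients, rounded.

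| c | Stemless n | D = 5: shift, error | D = 10: shift, error | D = 20: shift, error |
|---|---|---|---|---|
| 2% | 31 | 0.10, 5.2% | 0.20, 5.4% | 0.40, 5.9% |
| 5% | 30 | 0.25, 5.5% | 0.50, 6.1% | 1.00, 7.3% |
| 10% | 29 | 0.50, 6.1% | 1.00, 7.3% | 2.00, 10.4% |

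Example for the last cell: SE = 20 × √(1/29 + 1/32) = 5.13 and shift/SE = 2.00/5.13 = 0.39, which gives 10.4%.

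If D = 0 the shift is zero at every c. The only cost is then lost patients: power falls from 79.6% to 77.8% at c = 10%.

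**3. The same patients analysed as randomised.** Suppose those who cannot take the stemless implant receive a stemmed one and are counted in the stemless arm.

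- Stemless arm: (1 − c)(μ − 12.5) + c(μ − D)
- Stemmed arm: (1 − c)μ + c(μ − D)
- Difference: −12.5 + 12.5c

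The shift is 12.5c: 0.25, 0.625 and 1.25 points at c = 2%, 5% and 10%. With 32 per arm the chance of declaring non-inferiority is 5.5%, 6.4% and 8.1%. Comparing cD with 12.5c, per-protocol is the more lenient analysis only when D exceeds 12.5.

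**The case against.** **The article may be incomplete here.** It condenses a fuller protocol and does not call per-protocol the only analysis. Definitions commonly sit in a document not shown, so a missing definition would not be a finding by itself. What stands is that the article's own statistical section chooses a population for the non-inferiority conclusion, and the one it names is per-protocol.

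**One-sided loss is an inference.** A reader might infer that patients will be lost from the stemless arm alone and that the result must favour stemless. The documents do not support that. They describe no conversions, give no rate and do not say how a converted patient is classified. Stemmed patients can deviate too: the Background lists malpositioning, false route and periprosthetic fracture for the stemmed component. The bone-stock contraindication is listed for stemless but is not said to be unique to it. The direction also depends on prognosis, since D = 0 gives no bias.

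**The humerus is not wholly unseen before allocation.** Before then, "the patient will be referred to routine shoulder CT and MRI scans", and plain radiographs are taken. Only direct inspection comes later. Even so, no stated criterion uses the imaging to judge humeral bone.

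**An as-randomised analysis is diluted as well.** Step 3 of the working shows this is correct. A reader might conclude that per-protocol is simply the anti-conservative set here. That holds only for D above 12.5; at D = 10 the as-randomised analysis is the more lenient. This is a reason to require both analyses, not to replace one with the other.

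**The size is wholly assumed.** That is so. The 10.4% needs the top of both ranges together, and at c = 2% the error does not exceed 5.9%.

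**Conclusion.** The concern holds in a limited form. The plan rests its non-inferiority conclusion on a per-protocol set that it does not define, with no as-randomised analysis beside it, and its own text shows a route by which exclusions could differ between arms. Under assumed c of 2–10% and D of 5–20 points, the shift is 0.1–2.0 points and the one-sided type I error is about 5.2–10.4% instead of 5%. These figures assume SD 20, 32 evaluable patients per arm before exclusions, exclusion from the stemless arm only, and the same deficit D under either implant. They show what could happen and do not estimate what will. A definite bias in favour of stemless is not established. This is a low-cost improvement to the primary analysis; it does not show that the design fails.

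**What to change.** In Data analysis:

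1. Add an as-randomised analysis: all randomised patients with outcome data, grouped by allocated implant, whatever was inserted or later revised.
2. Define per-protocol membership, including how an intraoperative change of implant and a later revision are classified, and fix it for each patient blind to outcome.
3. Conclude non-inferiority only if the lower limits of both analyses exceed −12.5.

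The chance of a false conclusion under the joint rule cannot exceed the smaller of the two separate chances, so the rule protects whichever analysis is the more lenient. It does not by itself bring the error back to 5% when both are shifted.

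The Background and the Exclusion criteria should also be reconciled on metaphyseal bone stock. How that is done is a clinical matter for the investigators.

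The cost is one more analysis of data already collected and slightly lower power, because both analyses must succeed.

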## Outcome measures

The primary outcome will be the Western Ontario Osteoarthritis Shoulder (WOOS) score at 12 months [15].

The secondary outcomes will measure the following:WOOS score at three months;OSS at 3 and 12 months postoperatively [16];General health status questionnaire EQ-5D at 3 and 12 months [17].

At baseline, three-, and twelve-month visits, patients will fill out questionnaires, WOOS, OSS, and EQ-5D, alone before leaving the hospital (at the second visit after accepting participation) and in the waiting room (at three- and twelve-month visits) without interference from the medical staff.

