## Statistical analysis plan

### Sample size and power calculation

No existing studies report the minimal clinically important difference (MCID) of WOOS, but the MCID of the OSS was investigated and found to be 6 points or 12.5% of a maximum score [26]. By extrapolating MICD from OSS to WOOS, based on the known MCID for OSS, we estimated the accepted clinically meaningful change (ACMC) of WOOS to 237.5 points (12.5%).

With an ACMC of 12.5% and a standard deviation (SD) of ±20.0, which we found from our retrospective evaluation of patients operated with stemless TSA in our department, we need to include 64 patients, 32 in each group, to be 80% sure that the lower limit of a one-sided 95% confidence interval will be above the non-inferiority threshold of – 12.5%. With a loss of follow-up assumption of 20%, a total of 78 patients is required [27].

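### The Data analysis section does not carry over the non-inferiority criterion and conflicts with it: outcomes are compared by two-tailed tests of difference, which do not test the stated null hypothesis

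*Protocol article*

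**What the plan says.** The Study design section of the protocol article describes a "non-inferiority, randomized controlled clinical trial". Under Outcome measures, "The primary outcome will be the Western Ontario Osteoarthritis Shoulder (WOOS) score at 12 months". The Sample size and power calculation section sets a margin of 12.5% of the WOOS maximum (237.5 of 1900 points). It sizes the trial "to be 80% sure that the lower limit" criterion is met, namely that "the lower limit of a one-sided 95% confidence interval will be above the non-inferiority threshold" of -12.5%. The Hypotheses section then states the null and the alternative for one-year mean WOOS, both containing the margin.

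The Data analysis section says how the groups will be compared: "Differences in demographic data and outcome measures between the two groups will be compared using chi-square test for categorical variables". Student's t or Mann–Whitney U is the "test for continuous variables depending on the nature of data". Significance is P < 0.05, and all P "values are two-tailed". This section mentions no margin, no confidence interval and no one-sided level. Its only link to the non-inferiority design is the per-protocol analysis, for which it refers to the CONSORT extension.

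**The concern.** One primary outcome is left with two statements that do not fit together. The sample size and hypotheses require a confidence limit for a mean difference, compared with a margin at one-sided 5%. The Data analysis section names tests of zero difference at two-tailed 5% for outcome measures in general.

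A test of zero difference does not test a null hypothesis that contains a margin. A significant result can be compatible with non-inferiority, and a non-significant one does not establish it. If Mann–Whitney is chosen, there is no mean difference to compare with 12.5 points, although the hypotheses concern means.

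The trial's single confirmatory conclusion is at stake. An analyst following the Data analysis section literally would not produce the quantity on which that conclusion depends. The level matters too, because the sample size was derived for one-sided 5%.

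**Working it through.** **Inputs** (protocol article). From Sample size and power calculation: margin 12.5 percentage points, SD 20.0 (taken as percentage points), power 80%, one-sided 95% limit, 32 per group. From Randomization: two equal groups. From Data analysis: P < 0.05, two-tailed. The true difference is not stated; I assume 0, which reproduces the stated number.

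**1. The plan's own figure.** n per arm = 2 × (z₁₋α + z₁₋β)² × SD² / margin².

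- One-sided 5%: 2 × (1.6449 + 0.8416)² × 400 / 156.25 = 31.65, so 32 per arm and 64 in total. This matches the protocol.
- SE at 32 per arm = 20 × √(2/32) = 5.0, and margin/SE = 2.5.
- Power = Φ(2.5 − 1.645) = 80.4%. The noncentral t gives 79.6%.

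The stated 64 therefore rests on one-sided 5%.

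**2. Conditional: two-tailed 5% applied to the margin (two-sided 95% CI).**

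- n per arm = 2 × (1.9600 + 0.8416)² × 400 / 156.25 = 40.19, so 41 per arm and 82 in total. The t calculation gives 42 per arm.
- Power at 32 per arm = Φ(2.5 − 1.960) = 70.5%. The noncentral t gives 69.2%.

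**3. Conditional: P > 0.05 on a two-tailed test read as non-inferiority.** Suppose stemless is truly worse by the full 12.5 points.

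- 32 per arm: P(not significant) = Φ(1.96 − 2.5) − Φ(−1.96 − 2.5) = 29%. By noncentral t it is 1 − 0.692 = 31%.
- All 78 patients evaluable (39 per arm): 1 − 0.788 = 21%. By noncentral t it is 22%.

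The intended error at the margin is 5%.

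**4. How often the two rules disagree** (32 per arm, stemless minus stemmed, higher is better).

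- Non-inferiority by the one-sided limit needs an estimate above −12.5 + 1.645 × 5.0 = −4.3.
- The two-tailed test is not significant for any estimate within ±1.96 × 5.0 = ±9.8.
- Estimates from −9.8 to −4.3 are therefore not significant, yet non-inferiority is not shown. With truly equal arms the probability is Φ(−0.855) − Φ(−1.96) = 17%.

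**5. Direction of the scale.** The WOOS section makes 1900 the worst score and converts raw scores to a percentage of the maximum, without stating a reversal. On that percentage, W, higher is worse. The hypotheses and the −12.5% threshold make sense only if higher is better. With 100 − W, the difference stemless minus stemmed changes sign. A lower limit above −12.5 on the reversed scale is thus the same as an upper limit below +12.5 on W. Any corrected sentence must say which scale it uses. On W, a lower limit above −12.5 would not bound how much worse stemless could be.

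**The case against.** Three stronger conclusions are tempting.

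- **That the Data analysis section replaces the non-inferiority rule.** It does not. Sample size, hypotheses and data analysis all stand under the article's heading Statistical analysis plan. The one-sided criterion and the margin hypotheses are never withdrawn, and the Data analysis section itself refers to non-inferiority reporting guidance.
- **That the sample size is wrong.** Under the only success criterion the protocol states, 64 evaluable patients reproduce. The 70% power applies only if two-tailed 5% is carried into the margin comparison, and no section says so. A test of zero difference has no defined power for non-inferiority.
- **That the investigators will treat P > 0.05 as non-inferiority.** No section says this, and the hypotheses contradict it.

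The two statements could also coexist: the interval would decide the primary question, and two-tailed P values would be reported for baseline data, three-month WOOS, OSS and EQ-5D. The sentence on tests is generic and does not name the primary outcome. Blinded analysis limits any arm-driven choice between t and Mann–Whitney. An article may also leave the exact estimator to a fuller plan.

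These points narrow the finding but do not remove it. The Data analysis section fixes tests and sidedness for outcome measures without exempting the primary outcome. What it fixes conflicts with the criterion, so this is more than omitted detail. Blinding does not make a rank test yield a mean difference.

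**Conclusion.** The point holds as a conflict within the protocol. The non-inferiority criterion is stated for sizing and in the hypotheses. It is not carried into the section on outcome comparison, which prescribes tests that do not address the null hypothesis.

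The stated sample size is sound for one-sided 5%, given SD 20 and no true difference, apart from the small gap between the normal and t calculations. The figures of about 70% power and about 30% false passes show what is at risk if the Data analysis wording were applied to the primary outcome in those particular ways. They do not describe what the protocol says will be done.

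**What to change.** State the primary analysis in the Data analysis section, for example: *Non-inferiority on 12-month WOOS is concluded if the lower limit of the one-sided 95% CI (equivalently, of the two-sided 90% CI) for the mean difference, stemless minus stemmed, is above −12.5 percentage points, with WOOS expressed as 100 minus the percentage of the maximum raw score, so that higher is better.* If the unreversed percentage is kept, the condition becomes an upper limit below +12.5.

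Use a mean-difference analysis for the primary outcome, with no switch to Mann–Whitney. Confine two-tailed P < 0.05 tests to the other comparisons.

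This costs wording only; margin, design and the 64 evaluable patients are unchanged. If a two-sided 95% CI is preferred for the primary decision, the stated power must be lowered to about 70% at 64 evaluable patients. Keeping 80% would need about 82 evaluable patients (41 per arm by normal approximation).

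### The planned t-test or Mann–Whitney comparison of 12-month WOOS is valid but unadjusted; using the baseline score and the randomisation factors would gain precision without new data

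*Protocol article*

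**What the plan says.** The Outcome measures section fixes the endpoint: "The primary outcome will be the Western Ontario Osteoarthritis Shoulder (WOOS) score at 12 months". It also states that "At baseline, three-, and twelve-month visits, patients will fill out questionnaires, WOOS, OSS, and EQ-5D". The Eligibility section puts the baseline questionnaires at the second visit, after consent, while Randomization and concealment of allocation places the allocation in the operating room. Baseline WOOS is therefore a pre-randomisation measurement.

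The same randomisation section describes blocks of four, "balanced according to age in years (18–49, 50–59, 60–69, 70–79, 80–89, 90–110), sex, and ASA score".

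The Data analysis section, under the article's own heading for the statistical analysis plan, names the comparison: "Differences in demographic data and outcome measures between the two groups will be compared using chi-square test for categorical variables", and then a Student's t or Mann–Whitney U "test for continuous variables depending on the nature of data". That sentence covers the outcome measures and so the primary outcome. The article nowhere mentions a regression model, an analysis of covariance, a change score or a stratified analysis.

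Sample size and power calculation uses a margin of 12.5%, an SD of 20.0, 80% power and a one-sided 95% confidence interval. This gives 32 per group, 64 in all, and 78 after a 20% allowance for loss.

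**The concern.** A baseline value of the outcome is often its best single predictor. Here it is already collected, and the named test does not use it. The part of the 12-month variance that baseline explains stays in the standard error, and any chance difference in baseline WOOS passes into the estimated difference.

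The balancing factors raise a related point. If age, sex and ASA predict the outcome, balancing on them makes the true sampling variation of the difference smaller than a two-sample test assumes. An analysis that ignores them is then somewhat conservative.

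At stake is the width of the interval on which the non-inferiority conclusion rests, in a trial sized at 80% power with nothing to spare. The validity of that conclusion is not in question.

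**Working it through.** **Inputs.** Margin 12.5, SD 20.0, one-sided level 0.05, power 80%, 32 evaluable per arm (Sample size and power calculation). The correlation r between baseline and 12-month WOOS is not in the article; 0 to 0.5 is assumed.

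**Reproducing the plan's figure.** n per arm = 2 × (1.645 + 0.842)² × 20² / 12.5² = 31.7, so 32 per arm and 64 in total, as stated. The trial is thus sized for an unadjusted comparison. For the allowance for loss, 32 × 1.2 = 38.4, or 39 per arm, gives the stated 78.

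**Power of the planned test.** SE = 20 × √(2/32) = 5.00. Power = Φ(12.5/5.00 − 1.645) = Φ(0.855) = 80.4% (79.6% by the noncentral t distribution).

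**Power with baseline adjustment.** Residual SD = 20 × √(1 − r²). Power = Φ(12.5 / (SD × √(2/32)) − 1.645). The equivalent unadjusted size per arm is 32/(1 − r²).

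| Assumed r | Residual SD | Power at 32 per arm | Equivalent unadjusted n per arm |
|---|---|---|---|
| 0 | 20.0 | 80.4% | 32 |
| 0.2 | 19.6 | 81.8% | 33 |
| 0.3 | 19.1 | 83.5% | 35 |
| 0.4 | 18.3 | 86.1% | 38 |
| 0.5 | 17.3 | 89.3% | 43 |

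**Simulation including the balancing factors.** 78 patients were allocated in blocks of four within age × sex × ASA cells, with an assumed case mix and three assumed ASA levels. About 64 were evaluable, the test was one-sided at 5%, and each setting had 6,000 runs. The adjusted model contained baseline, age, sex and ASA as main effects.

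| Correlation of outcome with baseline / with factors (assumed) | Type I error, unadjusted / adjusted | Power, unadjusted / adjusted |
|---|---|---|
| 0 / 0 | 0.054 / 0.054 | 78.8% / 77.6% |
| 0.3 / 0 | 0.054 / 0.055 | 79.3% / 81.4% |
| 0.3 / 0.3 | 0.046 / 0.052 | 79.9% / 84.2% |
| 0.5 / 0.3 | 0.047 / 0.050 | 80.0% / 90.5% |

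The simulation error of a type I rate near 0.05 is √(0.05 × 0.95/6000) = 0.003. The conservatism of the unadjusted test (0.046 to 0.047) is therefore in the expected direction but small, and within about 1.5 simulation errors of nominal. If nothing in the model is prognostic, adjustment costs about one point of power.

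**The case against.** The strongest reply is that nothing here is wrong. An unadjusted comparison of a randomised continuous outcome is valid, the sample size was computed for it, and it delivers the stated power. A journal article also condenses, and covariates are often specified in a fuller plan. The first part stands, which makes this an improvement and not the correction of an error. The second carries less weight, because the article does not leave the method open: it names the test for the outcome measures and sizes the trial to match.

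The size of the gain also rests on a correlation that the article does not report. That stands too, and is why the range must include 0.2, where the gain is about 1.4 points.

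A reader might infer more from the randomisation section: that the cells are so sparse that balance fails, and that the analysis or the scheme must repair this. The article does not support that reading.

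- It gives no number of ASA levels. Two to five levels would give 6 × 2 × 2 = 24 to 6 × 2 × 5 = 60 cells, or 3.3 to 1.3 patients per cell. If minimisation was meant, the argument weakens further.
- What sparse blocks visibly disturb is arm size, and covariate adjustment does not correct arm size.
- Unequal arms cost almost nothing. With 29 and 35 evaluable, SE = 20 × √(1/29 + 1/35) = 5.02 and power = Φ(12.5/5.02 − 1.645) = 80.1%, against 80.4%.
- With 36 cells, the simulated SD of the arm-size difference was 4.7 to 5.6 patients, against √78 = 8.8 under simple randomisation. The scheme does improve size balance.

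Nor do the documents give a reason to change the strata during recruitment or to require a hospital term.

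**Conclusion.** The point holds as an efficiency improvement. The planned test is unbiased and reaches about 80% power. It gives up the share r² of the variance: 4%, 9%, 16% or 25% for r of 0.2, 0.3, 0.4 or 0.5. In power that is about 1 to 9 points at 64 evaluable patients. A further small gain is possible if age, sex and ASA are prognostic.

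This assumes the article's SD of 20, a one-sided 5% level and 32 evaluable per arm. The correlation is an assumption throughout, and at 0.2 or below the benefit is negligible. It would be wrong to conclude that the unadjusted result would be biased, that the trial is underpowered for its stated calculation, or that the randomisation scheme has failed. The two-tailed P values in Data analysis, which sit beside a one-sided interval in the sample-size section, are a separate matter and add no weight here.

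**What to change.** Before unblinding, state in the analysis plan that the primary estimate is the arm coefficient from a linear model of 12-month WOOS (as a percentage of maximum) on arm, baseline WOOS on the same scale, age as a continuous variable, sex, and ASA class in a few categories. Enter these as main effects only, not as one term per randomisation cell. Compare the model's one-sided 95% confidence limit with the 12.5% margin. Use the same form for OSS and EQ-5D scores, each with its own baseline. The unadjusted comparison can be kept as a supporting analysis.

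This also removes, for the primary outcome, the data-dependent choice between a t-test and a Mann–Whitney test; the latter gives no confidence limit for a mean difference to set against the margin.

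The cost is wording in the plan, a few degrees of freedom, and about one point of power if no covariate proves prognostic. No new data are needed. Keep the total at 78 and treat any gain as reserve; leave the randomisation scheme unchanged.
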